## Abstract

**Background:**

People with substance use disorders are vulnerable to acquiring HIV. Testing is fundamental to diagnosis, treatment, and prevention; however, in the past decade, there has been a decline in the number of substance use disorder (SUD) treatment programs offering on-site HIV testing. Fewer than half of SUDs in the United States offer on-site HIV testing. In addition, nearly a quarter of newly diagnosed cases have AIDS at the time of diagnosis. Lack of testing is one of the main reasons that annual HIV incidences have remained constant over time. Integration of HIV testing with testing for HCV, an infection prevalent among persons vulnerable to HIV infection, and in settings where they receive health services, including opioid treatment programs (OTPs), is of great public health importance.

**Methods/Design:**

In this 3-arm cluster-RCT of opioid use disorders treatment programs, we test the effect of two evidence-based “practice coaching” (PC) interventions on: the provision and sustained implementation of on-site HIV testing, on-site HIV/HCV testing, and linkage to care. Using the National Survey of Substance Abuse Treatment Services data available from SAMHSA, 51 sites are randomly assigned to one of the three conditions: practice coach facilitated structured conversations around implementing change, with provision of resources and documents to support the implementation of (1) HIV testing only, or (2) HIV/HCV testing, and (3) a control condition that provides a package with information only. We collect quantitative (e,g., HIV and HCV testing at six-month-long intervals) and qualitative site data near the time of randomization, and again approximately 7–12 months after randomization.

**Discussion:**

Innovative and comprehensive approaches that facilitate and promote the adoption and sustainability of HIV and HCV testing in opioid treatment programs are important for addressing and reducing HIV and HCV infection rates. This study is one of the first to test organizational approaches (practice coaching) to increase HIV and HIV/HCV testing and linkage to care among individuals receiving treatment for opioid use disorder. The study may provide valuable insight and knowledge on the multiple levels of intervention that, if integrated, may better position OTPs to improve and sustain testing practices and improve population health.

## Background

In its ongoing recognition of HIV testing as a fundamental component of HIV treatment and prevention, the latest 2022 National HIV/AIDS Strategy (NHAS) continues to encourage the expansion of HIV testing to nonclinical and nontraditional settings throughout the United States (U.S.), emphasizing the public health significance of all people with HIV (PWH) knowing their status (1). Despite recommendations from the US Preventive Services Task Force (USPSTF) that all adolescents and adults be screened for HIV in health care settings (2), less than half (43%) of U.S. adults have ever been tested for HIV (3). In addition, of the estimated 1.2 million PWH in the U.S., approximately 13% are unaware of their HIV status (4), individuals unaware of their infection status are is estimated to contribute to over one-third (35%) of new HIV transmissions (5, 6).

Lack of testing is considered one of the main reasons that annual HIV incidence in the U.S. has remained steady at more than 30,000 cases over the last decade (7). The COVID pandemic exacerbated already suboptimal HIV testing efforts and led to a massive hindrance of HIV testing efforts. Over the first one-year period of the pandemic alone (2019 – 2020), the Centers for Disease Control and Prevention (CDC) reported a significantly sharp decrease in testing in both healthcare (43%) and non-healthcare settings (50%) (8). The CDC and World Health Organization (WHO) have continued to call for expanding HIV testing in settings where persons vulnerable to HIV infection receive health services, including opioid treatment programs (OTP). In addition, the 2022 NHAS called for targeted HIV efforts and resources that specifically prioritize five populations that bear disproportionately higher HIV burden, one of which is persons who inject drugs (PWID) (1). PWID account for approximately one in ten incident HIV cases (9), with many citing socioeconomic barriers (e.g., homelessness, incarceration) hindering the ability of PWID to access prevention and treatment services for both HIV as well as substance use (10).

Given the populations of people who are vulnerable to HIV due to injection and non-injection use of drugs, outpatient substance use disorder (SUD) treatment centers and OTPs are well-positioned to implement routine HIV testing and diagnose incident cases early in the infection trajectory. In addition, prior research has shown both the feasibility (e.g., improvements in testing rates and receipt of test results compared to off-site referrals) and economic value of on-site HIV testing in SUD treatment programs (11–13). Yet, despite the need, feasibility and value of on-site HIV testing in these viable settings, most programs do not offer testing, with less than half of U.S. SUD programs and less than one-third of OTPs offering on-site HIV testing (14). Prior research has noted many significant organizational-level and client-level barriers preventing widespread HIV testing uptake in these treatment settings, including lack of reimbursement and insufficient billing systems, constraints surrounding staffing, resources, training and workflow, and concerns about delivering HIV test results and linkage to care (14–16). In addition, research has shown greater prioritization and perceived need for Hepatitis C virus (HCV) testing compared to HIV testing, given the higher prevalence of HCV compared to HIV within this population (17, 18). Additionally, the percentage of individuals with chronic HCV infection who are unaware of their infection (approximately 40%) is higher than those with undiagnosed HIV (19). Despite the availability of better-tolerated, shorter-duration HCV curative treatments, recent CDC data in the U.S. has shown that the number of people with HCV who have initiated treatment has declined over the past few years (19). Therefore, offering on-site testing services for HCV and HIV has been touted as being more relevant to OTPs than offering on-site testing services for HIV alone. The joint offer of HIV and HCV testing in OTPs (20) is particularly salient, considering that approximately 90% of PWID who seek care in traditional healthcare settings, i.e., non-substance use-related treatment, do not receive any HIV/HCV testing at their clinical visit (21). As such, more integrated approaches in OTPs may enhance key testing opportunities for high-risk populations to improve the identification of HIV and/or HCV and subsequent active referral for care.

Within this context, the objective of our 3-arm randomized controlled trial (RCT) “*Project I Test: Implementing HIV Testing in Opioid Treatment Programs*” is to focus on addressing commonly cited organizational-level barriers to widespread HIV testing in OTP settings, as well as examine whether the offer of HCV testing in conjunction with HIV testing serves as a motivator for implementation of HIV testing. These goals align with the current NHAS strategy to develop new and expanded implementation of effective, evidence-based, or evidence-informed models for HIV testing that improve convenience and access (1). The approach we adapted, implemented, and are currently assessing through this RCT utilizes “practice coaching” (PC), a low-intensity, evidence-based, hands-on approach used to guide implementation of a change initiative, with the change initiative in this study being increased on-site HIV testing in OTPs. PC has been used to implement change in healthcare practices that improve client outcomes, largely through care delivery in primary care settings including increasing preventive service delivery rates, assisting with chronic disease management, and implementing system-level improvements within practice settings (22–26). The two active PC intervention approaches in this RCT were designed to improve the initial and sustained implementation of on-site HIV testing and linkage to care among OTP clients either alone or in conjunction with HCV testing; rates of HIV testing and linkage to care (as well as their associated cost-effectiveness) of the two PC interventions can then eventually be compared incrementally to one another as well as to an information-only control condition. The purpose of this paper is to discuss these approaches, as well as outline the overall protocol of our Project I Test study, which to our knowledge is the first study to test organizational approaches to increase uptake of HIV and HIV/HCV testing and linkage to care within community-based outpatient programs that provide opioid use disorder (OUD) treatment. Therefore, this study has critical public health implications for understanding how OTP settings can best be supported in the implementation of our innovation of interest (i.e., offering HIV testing on-site and linking PWH to care) and in their sustainment of these improvements, with the ultimate goal of improving HIV-related health outcomes for clients receiving opioid treatment.

### Study Objectives:

The **primary objective** of the study (Project I Test) is to evaluate the uptake of HIV testing at OTPs, following the implementation of interventions that include practice coach facilitated structured conversations around implementing change, along with provision of relevant resources and documents to support the implementation of (1) HIV testing only, or (2) HIV/HCV testing, and (3) a control condition that provides a package with information only. The **secondary objectives** of the Project I Test study are to evaluate: the incremental impact of the HIV/HCV intervention (e.g., proportion of OTP clients tested) on the implementation of HIV testing, compared with the HIV only intervention, and during the initial impact period; the effectiveness of the interventions relative to the control condition, on the sustained impact of HIV testing; and initial impact of HCV testing and sustained impact of HCV testing. The **tertiary objectives** of the Project I Test study are to evaluate the effectiveness of the interventions relative to the control condition on linkage to HIV care among OTP clients who test positive for HIV; linkage to HCV care among OTP clients who test positive for HCV; change in perceived barriers/facilitators to HIV testing; and intervention impact mediated by change in perceived barriers/facilitators. Additional tertiary objectives include evaluating the organizational and environmental characteristics of OTPs that serve as facilitators and barriers to the provision of HIV testing, the sustained implementation of HIV testing, the uptake of testing by OTP clients, and providing timely linkage to care for persons who test positive. The **quaternary objective** is to assess the health outcomes, health care utilization, and cost-effectiveness of the PC interventions compared incrementally to one another and to the control condition. This will allow for assessing the budget required to implement (scale up and sustain) the PC interventions nationally.

## Methods/Design

### Study Design

This protocol manuscript follows the SPIRIT reporting guidelines (27). The design is a 3-arm cluster-RCT of sites treating opioid use disorder in the U.S. Fifty-one OTPs are randomly assigned to one of three conditions (17 sites per condition) – information only control arm, PC to initiate or increase HIV testing and linkage to care, and PC to initiate or increase HIV and HCV testing and linkage to care (Figure 1). The study tests the effect of two active evidence-based PC interventions against an informational control on the provision and sustained implementation of on-site HIV testing and linkage to care, and on-site HIV/HCV testing and linkage to care, among OTP clients.

### Randomization

Sites are randomized into three groups (HIV PC, HIV/HCV PC, and information only control condition) in a ratio of 1:1:1 using a blocked randomization scheme to ensure relative balance across time of entry into the study. The data analyst, who is not involved in the delivery of the intervention, keeps the randomization schedule and sequence secure, and ensures confidentiality and independence of the allocation data. After site personnel complete baseline surveys and interviews, site personnel are notified to which of the three study conditions the site has been assigned.

### Eligibility criteria

Site eligibility criteria for this study are: 1) OTP site sees at least 150 unduplicated clients per year; 2) The site is capable and willing to prospectively collect data on the number of clients who a) are offered any HIV and/or HCV tests; b) completed these tests; c) are referred to care/evaluation (and type of referral) if positive); and d) are linked to care/evaluation within 30 days of diagnosis of HIV and/or HCV; 3) The site is capable and willing to provide aggregate client testing data within demographic categories of gender and race/ethnicity and data on HIV/HCV test reimbursement processes and outcomes; 4) the site is able to select staff willing to consent to participate in study surveys, qualitative interviews, and intervention coaching throughout the study. Sites in which over 50% of clients served in the prior 6 months were HIV or HCV tested are excluded. To be eligible to participate in the study’s site surveys, interviews and intervention activities, individuals must be site personnel employed within one of the 51 enrolled sites.

### Study Settings and Recruitment

The sampling frame consists of all opioid treatment programs/sites in the 2017 National Survey of Substance Abuse Treatment Service (N-SSATS), a national census of all US substance use treatment facilities, that have a minimum client census of 150 clients per year. The study draws on a random sampling of 500 eligible sites from this sampling frame, and will draw additional sites as needed. A total of 51 eligible sites will be enrolled in the trial. Recruitment occurs through e-mail and telephone contact. Site leadership (e.g., Chief Executive Officer, Director) are contacted, informed about the study and invited to complete a screening process to determine the OTP’s eligibility to participate in the study. If interested in participating in the study, the site leader completes a brief screening by telephone interview (after providing verbal consent) or via self-administered survey to determine the site’s eligibility to participate. Enrollment consists of obtaining a signed form letter from each participating site, outlining the various study activities in which the site personnel will participate. The site leader must also complete an acknowledgment from noting that participation in the study is voluntary and that there will be no impact to any individual employee of the site for not participating. Participants in this study consists of the professional staff working at eligible treatment programs/sites around the country that treat clients with opioid use disorder. Staff at selected sites that accept the invitation to participate are interviewed and complete brief surveys to confirm that they meet eligibility criteria. We also recruit, via email, directors working at state substance use authorities. We will conduct a survey of state policies and guidelines relevant to HIV and HCV testing. To participate in state surveys, individuals must be directors at state substance use authorities in the participating sites’ states.

Sites complete all surveys and related evaluations according to the study timeline. Participants may retract their consent to participate in the study, and may do so at any time before or during the study. Once a site or staff member participating in the study withdraws from the study during treatment, their data is excluded from our specific analysis, but may inform aggregated analysis of data.

A number of procedures are in place to promote retention in the study for the duration of the planned intervention. The primary strategies to improve retention in the interventions in this trial are twofold. The first is our incentive structure. Participating sites receive monetary incentives during their 2-year involvement. The payments are given once after completing their initial data collection plan (typically within 2 weeks of randomization) and a second/final time after the site completes the second of four aggregate data transfers. Personnel questionnaires and interviews are compensated at $40 and $50 (respectively); per each site’s discretion, these incentives are either issued directly to the personnel completing them or pooled into a single site-wide incentive (e.g., staff luncheon). This is intended to prevent participants from providing partially completed questionnaires, not adhering to treatment as delivered, or withdrawing from the study after enrollment. Secondly, the PCs work with the sites to encourage them to participate and adhere to the intervention sessions/timeline/window. PCs are mindful and respectful of the sites’ time and busy schedules and therefore ensure that they meet their scheduling needs. The collaborative nature of the intervention helps as the PC will assist the site in setting goals/action items and help brainstorm and discover ways to implement change. Intervention adherence is part building relationships and part the site staff’s time and motivation. Contacting the site to encourage them and move them along is part of the success.

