## Outcomes

### Primary Outcome

The primary outcome analysis will compare the PC interventions with the control condition on the initial impact of HIV testing as measured by the proportion of OTP clients tested during the period 7–12 months after randomization (“initial impact”, T3), while controlling for HIV testing during the baseline period (T1).

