## Data Sources

We use various approaches to collect data to measure outcomes and covariates (see Table 3). Study sites, upon enrollment in the study, are provided with a spreadsheet which they may use to assist in compiling aggregate de-identified data summaries, including HIV/HCV testing data. These data are transferred from sites at 6- month intervals and are checked for consistency. We use REDCap Survey data capture tools, with automatic range and consistency checks for quantitative survey data collection. PCs track the intervention process and record these data in structured forms, i.e., Practice Coach Interaction Form (PCIF). Some of the intervention process data are collected and managed using REDCap, and other intervention process data are collected using electronic collection forms. Qualitative interview data, including audio recordings and transcriptions, are collected via digital audio recorders. All data are stored securely on an encrypted and password protect server. All personal data of participants, both program and staff, are assigned a unique identifier that is stored on a secure server available only to data analysts and researchers with approved access to the database. Data analysis will only include non-identifiable data. Prior to analyses of the site surveys, factor structure and reliability of scales will be documented and all variables will be assessed for appropriate statistical distributions for analysis. Any missing data will be accommodated using multiple imputation.

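### Data of sites that withdraw during treatment are excluded from an undefined "specific analysis", which breaks the as-randomized comparison and conflicts with the multiple-imputation rule

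*Protocol article*

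**What the plan says.** Study Settings and Recruitment first says that participants may retract consent at any time. It then sets the rule: "Once a site or staff member participating in the study withdraws from the study during treatment, their data is excluded from our specific analysis". The sentence goes on to allow such data a possible use in an aggregated analysis. Neither the specific nor the aggregated analysis is defined anywhere in the article.

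Data Sources says: "Any missing data will be accommodated using multiple imputation". In the SPIRIT checklist, item 20c (analysis population and missing data) points only to Page 25, Lines 553–554. Those are the last lines of the range cited for data collection and management (Page 24, Lines 536–554), so the item appears to refer to this imputation sentence. The article does not state that all 51 sites are analysed in the arm assigned.

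Sites are randomized "in a ratio of 1:1:1 using a blocked randomization scheme", 17 per arm, and learn their allocation after the baseline surveys and interviews. The checklist says there was no blinding. The primary outcome is "the proportion of OTP clients tested during the period 7–12 months after randomization" (T3), controlling for baseline (T1). It comes from aggregate site summaries: "These data are transferred from sites at 6- month intervals and are checked for consistency".

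**The concern.** The coaching or control period fills T2, and the primary outcome is measured in T3. A site that withdraws during treatment therefore leaves after randomization, knowing its arm, and before its primary outcome exists. If its data are then excluded, including T1 and T2 counts already delivered, the groups compared at T3 are no longer the groups that were randomized. With 17 clusters per arm, a few exclusions can move an arm's mean.

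Loss that differs between arms is plausible. Only coached sites carry about 16 sessions over about 29 weeks, while control sites receive information materials. The article also says that adherence depends partly on the time and motivation of site staff, which may also drive testing.

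The two rules give different analysis sets. A withdrawn site's T3 count is missing data, which Data Sources would impute, whereas Study Settings and Recruitment would remove the site. In an unblinded trial that choice should not be left open until the data are seen.

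**Working it through.** **Inputs from the article.** There are 17 sites per arm and about 100 clients per site per period. The ICC is 0.04 to 0.08. Testing is 20% (control), 30% (HIV coaching) and 41% (HIV/HCV coaching). Stated power for the primary outcome is over 95%. **Assumed by me:** two-sided alpha of 0.05, and the number and pattern of withdrawals.

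**Step 1: the plan's own figure.** Effective sample size per arm = 17 × 100 / (1 + 99 × ICC). This is 1700/8.92 = 190.6 at ICC 0.08 and 1700/4.96 = 342.7 at ICC 0.04. The pooled coaching rate is (30 + 41)/2 = 35.5%, a difference of 0.155 from control.

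Power = Φ[(0.155 − 1.96 × SE0) / SE1], with SE0 under a common rate and SE1 under the two separate rates.

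At ICC 0.08 the common rate is (0.20 + 2 × 0.355)/3 = 0.3033.
- SE0 = √[0.3033 × 0.6967 × (1/190.6 + 1/381.2)] = 0.0408
- SE1 = √[0.20 × 0.80/190.6 + 0.355 × 0.645/381.2] = 0.0379
- Power = Φ(1.98) = 97.6%

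The same steps give 99.4% at ICC 0.06 and above 99.9% at 0.04, so the stated figure reproduces. Losing 3 sites per coaching arm still leaves 96.7% at ICC 0.08. The issue is bias, not primary power.

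**Step 2: how exclusion moves a mean.** If d of 17 sites are excluded, the arm mean shifts by d/(17 − d) × (mean of all sites − mean of excluded sites). The multiplier is 2/15 = 0.133, 3/14 = 0.214 or 4/13 = 0.308 for d = 2, 3 or 4. The shift is zero if the excluded sites are typical, positive if they test less than average, and negative if they test more.

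**Step 3: simulation under no true effect.** Site rates were drawn from a beta distribution (mean 20%, ICC 0.04 or 0.08), with binomial counts for 100 clients per site. The 34 coached sites were compared with the 17 control sites by a site-level t-test, without T1 adjustment, in 4,000 runs per setting. From the 34 coached sites, 4, 6 or 8 were excluded (2, 3 or 4 per arm on average), and none from control. Three times as likely means that sites on one side of the median T3 rate have three times the withdrawal weight of those on the other.

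Each cell gives bias in percentage points and type I error, for ICC 0.04, then ICC 0.08.

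| Who withdraws | 2 per arm | 3 per arm | 4 per arm |
|---|---|---|---|
| Random | +0.1, 5.2%; 0.0, 4.9% | +0.1, 4.6%; 0.0, 5.0% | 0.0, 5.0%; +0.1, 5.6% |
| Low-testing 3 times as likely | +0.5, 5.5%; +0.7, 5.1% | +0.6, 6.0%; +1.0, 5.1% | +1.0, 5.8%; +1.2, 6.1% |
| Lowest-testing (worst case) | +1.7, 12.6%; +1.9, 10.2% | +2.4, 17.0%; +3.0, 14.8% | +3.2, 26.9%; +4.2, 24.7% |
| High-testing 3 times as likely | −0.4, 5.5%; −0.6, 5.4% | −0.7, 5.8%; −1.0, 6.4% | −1.0, 6.7%; −1.4, 6.2% |

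With all sites kept, the mean difference is 0.0. If low-testing sites are favoured for withdrawal equally in every arm (3 per arm, ICC 0.08), the bias is 0.0 and type I error 5.1%.

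Step 2 shows how strong the worst case is. At 3 per arm and ICC 0.08, a 3.0-point shift divided by 0.214 means that the excluded sites average about 14 points below the 20% mean, that is, about 6%.

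**The case against.** The strongest reply is that the sentence does not end at the exclusion. The primary outcome is built from aggregate site summaries, and data of withdrawn sites may inform aggregated analysis. On that reading the primary model might keep these sites. This stands as a possibility, but it does not rescue the rule: the clause is permissive, neither term is defined, and the primary analysis set would still be a matter of choice.

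The imputation sentence could be meant for gaps at sites that remain, since it follows text on site surveys. If so, the conflict is not strict. But the checklist appears to cite that sentence for the analysis population, and it says any missing data. If it does govern the primary analysis, it removes most of the concern, and the exclusion sentence is then the one to change.

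The rule covers withdrawal from the study during treatment and follows a sentence on retracted consent. A site that merely stops coaching is not clearly covered, and a site that retracts permission cannot have its data kept regardless.

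A reader might infer that the rule favours coaching. The documents do not show this. They give no withdrawal rates, coaches work to retain their sites, control sites may also leave, and the sign of the bias changes with who leaves.

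A reader might also infer that nothing is paid for T3, because site payments end "a second/final time after the site completes the second of four aggregate data transfers". Surveys and interviews scheduled in T3 are still paid, and nothing shows that payment timing causes loss. Moving the payment would also remove the incentive for the T2 transfer, so I do not propose it.

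Nor is the site the unit of analysis. It is the unit of randomization; the GEE models clients nested within sites.

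**Conclusion.** The point holds as a defect in a stated rule. As written, the protocol excludes randomized clusters on a post-randomization event in an unblinded trial, names two undefined analyses, and gives a second, conflicting instruction for missing data. It should be settled before the primary analysis.

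The size is uncertain. Over the patterns examined the bias runs from −1.4 to +4.2 points, set against a planned difference of 10 points between HIV coaching and control. Moderate selection gives about 1 point or less in most settings, with little inflation of type I error. Error rates of 10–27% arise only if the lowest-testing coached sites are the ones that leave. Bias towards coaching is plausible given the burden on coached sites, but it is not established.

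These figures rest on assumed withdrawal counts and patterns, no withdrawal in control (except in the equal-withdrawal case), and a simple site-level test instead of the planned GEE. They also omit the T1 adjustment, which would reduce the part of the bias that baseline testing explains.

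**What to change.** Reconcile Study Settings and Recruitment with Data Sources by replacing the exclusion sentence with one rule:

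- All 51 randomized sites are analysed in the arm assigned.
- Aggregate data delivered before withdrawal are retained, unless the site retracts permission for their use.
- Sites that stop coaching or withdraw are asked for their T3 and T4 aggregate counts, where they agree.
- Remaining missing site-periods are multiply imputed, with a sensitivity analysis for data missing not at random.
- The analysis that excludes withdrawn sites is a sensitivity analysis only.

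The undefined terms for specific and aggregated analysis should go, or be defined so that the primary analysis set is unambiguous.

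The cost is protocol and analysis-plan wording, follow-up requests to any withdrawn sites, and one added sensitivity analysis. No further sites are needed. The article reports that the trial is still collecting data, so the change is feasible.
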